#### The OPUS treatment in the experimental extension period (year 2-5)

The aim is to continue the original patients - primary team member relation in the extension period, if possible. Patient to staff member ratio is 15:1. Patients will still be offered treatment tailored to meet their individual needs. As a minimum the patients will receive at least one face-to-face contact each month with their primary team member, and at least one other contact (e.g., telephone, mail). Families can in the extension period still join the psycho-educational family treatment due to their needs, and will at minimum be invited to booster sessions of a survival skills workshop. Patients can participate in all group programmes available in OPUS. Within the resources of the team, there is no upper limit for the amount of treatment the individual patient may obtain.

The intensity of intervention will be registered. Interventions intensity will be extracted from the Danish Psychiatric Case Register. In case of doubt, data will be cross-validated with data extracted from the patient's medical record. Cost of intervention will be assessed with help from the economists in regional health authorities.

#### Standard treatment (year 2-5)

Patients, who after 11/2 years of OPUS treatment, are randomized to further half a year of the specialised assertive intervention, will be transferred to standard treatment after a total of two years OPUS treatment. Standard treatment can be either affiliation to a community mental health centre, assertive community treatment, or primary care, depending on the patient's needs. The most common will be referral to community mental health care centres, which usually offer the patient treatment in which home visits are possible but office visits are the general rule. The patient to staff member ratio varies between 20:1 and 30:1.

The transition from the OPUS treatment to standard treatment will be carried out gradually and as gentle as possible.

### Monitoring programme fidelity

Monitoring the fidelity of the intervention to OPUS treatment will be carried out by an independent investigator interviewing the six OPUS team leaders, using the index of fidelity to Assertive Community Treatment (IFACT)[16]. Assertive community treatment (ACT) and the OPUS treatment have some key elements in common. However, the OPUS interventions are enhanced by more specific content aimed at patients with first episode psychosis, including better family involvement and social skills training. To address these core elements we will develop a programme fidelity measure with special registration of presence or absence of critical components in the OPUS treatment. These elements are: primary contact to one member of the team, psycho-education, crisis plan, social skills training, rehabilitation support, psycho educational family treatment, and multifamily group.

### Outcome measures

The primary outcome measure is: negative symptoms measured with schedule for assessment of negative symptoms in schizophrenia (SANS[17]). Investigators at entry and at the 31/2 years follow-up interview will be independent and blinded for treatment allocation. Through training interviews, we will ensure that the assessors have a high level of interrater reliability with kappa values for primary outcome measure of at least 0.70, prior to beginning the trial. We will also ensure that assessors have an interclass correlation coefficient (ICC) of at least 0.70 regarding SANS global scores. ICC is calculated in SPSS using two-way mixed models for absolute agreement on single measures.

The secondary outcome measures are: simultaneously remission of both negative and psychotic symptoms, measured with SANS and schedule for assessment of positive symptoms in schizophrenia (SAPS[17]), psychotic symptoms measured as continuous measures, substance abuse, working alliance, self efficacy, user satisfaction, adherence to treatment, compliance with medication, suicidal behaviour, use of bed days, ability to live independently, and labour market affiliation. The criteria for remission are that none of the global measures of severity in SAPS (global scale for hallucinations, delusions, bizarre behaviour, or thought disorder) and SANS (global scale for anhedonia, avolition, alogia, and affective blunting) exceeds a value of 2 (2 = mild symptoms). All outcome measures are measured with validated scales (Table 1). These outcomes will be assessed at baseline and at follow-up. Through training interviews, we will also ensure that assessors have an ICC coefficient of at least 0.70 regarding SAPS global scores.

**Table 1 T1:** Assessment instruments in the OPUS-II trial.

Topic:	Instrument:
Psychopathology	Schedules for Clinical Assessment in Neuropsychiatry (SCAN)[28], Schedule for assessment of positive and negative symptoms in schizophrenia (SAPS and SANS[17])[29], Hamilton's depressions scale[30], Suicidal behaviour, DUP, Duration of Untreated Psychosis[31]

Social function	Personal and Social Performance scale, PSP[32] Global Assessment of Functioning, GAF[33]

Cognitive function	Brief Assessment of Cognition in Schizophrenia, BACS [34]

Medication and side effect	The UKU side effects rating scale, UKU[35] Patients self rapport

Selfefficacy	General Self - efficacy Scale[36]

Alliance	Working Alliance Inventory, client, WAI[37]

Quality of life	WHO Quality of Life, QOL[38]

Client satisfaction	Client Satisfaction Questionnaire (CSQ)[39]

Vital status, cause of death [18], use of beddays[19]	Danish national registers

Socio demographic information, labour market affiliation, civil status, cohabitation status, children, education, living in an institution for mentally ill, living in an institution for homeless[20]	Danish national registers

To be able to evaluate the external validity of the trial, we will furthermore register sex, age, diagnosis, medical treatment, substance abuse, and treatment adherence for the patients who do not participate in the trial.

#### Register-based information

vital status, cause of death [18], use of mental health services[19], living in an institution for mentally ill, living in an institution for homeless, labour market affiliation, sick leave, and early age pension will be extracted from the unique, complete, longitudinal Danish registers[20]. Use of antipsychotic medication will be extracted from the Danish Register of Medicinal Product Statistic[21].

#### Participant withdrawal

participants can withdraw his/hers informed consent from the trial at any time without any explanation. We have obtained permission from the Danish Data Protection Agency (journal number: 2009-41-3314) for register-based information for all randomized patients, and in analyses of this information, we will include data from all patients.

### Sample size calculation

In the OPUS I trial we found that the patients treated in OPUS had a mean score of 1.42 in negative dimension and patients treated in standard treatment had a mean score of 1.84 in negative dimension with standard deviation of 1.2[22,12]. In this present OPUS II trial we want to be able to detect a difference of 0.4 point in negative dimension, measured with SANS. We are thus planning a trial of a continuous response variable from independent control and experimental participants with one control per experimental participant. If the true difference in the experimental and control means is 0.4 with a standard deviation of 1.2, we will need to study 142 experimental participants and 142 control participants to be able to reject the null hypothesis that the population means of the experimental and control groups are equal with probability (power) 0.80. The type I error probability associated with this test of this null hypothesis is 0.05, and 200 patients will be included in each intervention group because we expect approximately 30% attrition.

### Data analyses

The primary outcome measure, negative symptoms, will, as other continuous outcome measures, be subjected to analysis using a mixed-model analysis with a repeated measurements model with unstructured variance matrix, using the mixed-model command in SPSS. This approach assumes that the distribution of missing data can be estimated from the information from previous interviews and from information about other patients in the database. The condition for using this method is the assumption that data are missing at random or missing completely at random when taking into consideration the information extracted from baseline interviews and information about the other patients in the database. In this model, baseline values of the scales are included. Variables included as covariates will be site (six different teams), sex, co-morbid substance abuse, baseline values of the remission variable, and the baseline values of variables that differ significantly in drop-out analyses. Besides the above-mentioned variables, compliance with medication, level of school education, and whether or not a family member is involved in treatment will be included in analyses of differences between patients that are lost to follow-up and those who remain in the trial. If significant, these variables will be included as covariates.

For evaluation of the dichotomous secondary outcome measure (simultaneously remission of psychotic and negative symptoms or not), we will use multiple multivariate imputations, using all other covariates to impute a distribution of missing values. The dichotomous outcomes will be analysed with logistic regression analyses. Variables included as covariates will be the same as those included in analyses of continuous measures. Similar to the repeated measurement, the condition for using multiple imputations is that data are missing at random or missing completely at random, when taking into consideration the information extracted from baseline interviews and information about the other patients in the database.

Analysis will be based on the intention-to-treat principle. Data from all patients will be included in the group to which random assignment is made, regardless of intervention received.

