### Randomisation

Randomisation will be centralised and computerised with concealed randomisation sequence carried out by the Copenhagen Trial Unit (CTU). Block size will be unknown to the investigators and clinicians. Randomisation will be stratified for treatment site (six sites) and severity of global score on the four of the five domains in SANS, anhedonia, avolition, alogia and affective blunting, with distinction between at least one of the global score measured less than 3 compared to 3 or more. Signed informed consent will be obtained prior to patients being randomized. The allocations concealment is ensured by the investigators call to the randomisation unit, CTU, after completing the collection of baseline data and data needed for the randomisation.

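### The SANS severity stratum used in randomisation is not among the named covariates, and its two levels overlap as worded; the effect on the primary analysis is negligible, but both need correcting

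*Protocol article*

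**What the plan says.** The Randomisation section of the protocol article gives two stratification factors: "Randomisation will be stratified for treatment site (six sites) and severity of global score on the four of the five domains in SANS". The four domains used are affective blunting, alogia, avolition and anhedonia. The severity factor is split "with distinction between at least one of the global score measured less than 3 compared to 3 or more".

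The Data analyses section lists the covariates for the continuous outcomes: "Variables included as covariates will be site (six different teams), sex, co-morbid substance abuse, baseline values of the remission variable", followed by baseline variables that differ between drop-outs and completers. The sentence before that list reads "In this model, baseline values of the scales are included". For the dichotomous outcomes, "Variables included as covariates will be the same as those included in analyses of continuous measures".

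The Outcome measures section defines remission. No SAPS global score (hallucinations, delusions, bizarre behaviour, thought disorder) may be above 2, and the same limit holds for the same four SANS domains: none of "SANS (global scale for anhedonia, avolition, alogia, and affective blunting) exceeds a value of 2 (2 = mild symptoms").

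**The concern.** There are two separate defects.

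**The analysis carries only one of the two stratification factors.** Stratified allocation makes the arms more alike on the stratifying variables. A model that leaves out a prognostic stratifier does not credit that balance, so its tests tend to be conservative. The article sets out an explicit list that names site and omits the SANS stratum, so this is more than a detail left for later.

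**The stratum rule does not split patients into two groups.** If 'at least one' applies to both halves of the sentence, any patient with a mixed profile belongs to both levels. If it applies only to the first half, the split is any score below 3 against none below 3. The remission definition, which cuts the same four domains between 2 and 3, suggests a third version: all four at 2 or less against at least one at 3 or more. The stratum used in the analysis has to be the one used for allocation, and the text does not say which that was.

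**Working it through.** **1. The plan's own sample size.** Inputs from the Sample size calculation section: "If the true difference in the experimental and control means is 0.4 with a standard deviation of 1.2", "with one control per experimental participant", power 0.80, type I error 0.05 (two-sided reproduces the figure).

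n per arm = 2 × (1.960 + 0.842)² × 1.2² / 0.4² = 141.3, rounded up to 142. This agrees with the article. Its 200 per arm corresponds to 1 − 142/200 = 29% attrition. Nothing below alters these figures.

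**2. Overlap of the strata.** Assume integer global scores 0 to 5 on four domains.

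- All patterns: 6⁴ = 1,296.
- All four below 3: 3⁴ = 81. All four at 3 or more: 3⁴ = 81.
- Mixed patterns: 1,296 − 81 − 81 = 1,134.

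The mixed patterns fit both levels if 'at least one' governs both. They also change sides between the two mutually exclusive readings:

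| Reading | Milder level | Severer level |
|---|---|---|
| All four ≤2 v at least one ≥3 | 81 | 1,215 |
| At least one <3 v none <3 | 1,215 | 81 |

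These are counts of possible patterns, not shares of patients. The article gives no distribution of baseline scores.

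**3. How far baseline remission stands in for the stratum.** Take the stratum as all four ≤2 v at least one ≥3.

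| SANS stratum | SAPS globals | Baseline remission |
|---|---|---|
| At least one ≥3 | any | no |
| All four ≤2 | all ≤2 | yes |
| All four ≤2 | at least one ≥3 | no |

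Only the last row separates the two variables. In the simulation below, the severe stratum held about 40% or 60% of patients and remission 35% or 26%. That leaves 1 − 0.40 − 0.35 = 25% or 1 − 0.60 − 0.26 = 14% of patients in the last row. The correlation between stratum and remission was −0.60 or −0.72.

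**4. Effect on the primary SANS analysis.** Simulated: 400 patients randomised in permuted blocks within 6 sites × 2 SANS levels, 284 analysed, 1,500 runs per setting, linear models for follow-up SANS. Assumptions not in the document: block size 4, correlation 0.5 between the latent domain scores, baseline-to-follow-up correlation 0.3 to 0.7, the stratum shares above, and a direct stratum effect of 0 or 0.3 points beyond baseline SANS. Sex and substance abuse were left out.

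| Quantity | Site + baseline SANS + baseline remission | Same + stratum |
|---|---|---|
| SE, r = 0.5, no direct effect, severe share 60% | 0.1239 | 0.1241 |
| SE, r = 0.5, direct effect 0.3, severe share 40% | 0.1247 | 0.1243 |
| Type I error over all settings | 0.038–0.059 | 0.041–0.061 |

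The ratio of SE without the stratum to SE with it was 0.9985 to 1.0039, a change of −0.15% to +0.4%. With 1,500 runs, the Monte Carlo standard error of a 5% rejection rate is √(0.05 × 0.95 / 1,500) = 0.0056, so both type I ranges are compatible with 0.05 or very close to it.

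**5. Outcomes other than SANS.** These were not simulated, because the document gives no relation between them and the SANS stratum. One indirect indication: with the SANS outcome and only site and baseline remission in the model (no baseline SANS), type I error was 0.040 to 0.054, so remission alone already recovered most of the stratum's information.

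**The case against.** A reader might infer that the omission makes the trial's standard errors materially too large. The document does not support this for the primary outcome. The sentence just before the covariate list puts the baseline scale values into the model, and the two-level stratum is a coarse cut of those same scores. A clear loss appeared only in a model with site and no baseline SANS or remission, where the SE was 4% to 50% larger than in the full model. That is not the planned model. A formula based on the share of variance that the stratum explains by itself has the same flaw: what counts is the share it adds after the planned covariates. This objection stands.

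A reader might also infer that the stratification on severity achieves almost nothing. That takes the most adverse literal reading and adds invented score distributions. Allocation is computerised at an external trial unit, which must place each patient in one level, and the remission definition makes the intended cut easy to guess. The inference fails, but the wording still does not say which rule was used.

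Further points on the other side are fair. Remission is adjusted for its own baseline value, and SAPS for its own baseline scale. In logistic regression an added covariate need not reduce the SE. Any error from the omission is conservative. These limit the size of the point but do not remove it: baseline remission mixes the two SANS strata whenever SAPS decides, so it is not the allocation factor.

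**Conclusion.** Both defects stand on the text. The fixed covariate list carries site but not the SANS stratum, and the two SANS levels are not mutually exclusive as written.

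For the primary outcome the consequence is negligible: an SE change of −0.15% to +0.4%, under the simulation assumptions and with the baseline SANS score in the model as the article states. Sample size and power are unaffected.

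For outcomes other than SANS (for example SAPS, working alliance, self efficacy, bed days and labour market affiliation) the analysis does not fully reflect the randomisation. Any loss is probably small and in the conservative direction. It cannot be quantified from the document, since the added prognostic value of the stratum for those outcomes is not given.

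The stratum wording is an error to correct, not evidence that allocation went wrong.

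**What to change.** - Add the SANS severity stratum, as allocated, to the covariates of every continuous and logistic model alongside site. This costs one degree of freedom per model.
- Ask the trial unit which rule was programmed, then restate it as two mutually exclusive levels. If it is the cut used in the remission definition, the wording would be: all four SANS global scores 2 or less, versus at least one score of 3 or more. If another rule was programmed, describe that one, so that the stratum in the analysis is the one used for allocation.

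The cost is one enquiry to the trial unit and one sentence each in the Randomisation and Data analyses sections. Recruitment and sample size are untouched.

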### Feasibility

We plan to recruit 400 patients for the trial from 2009 to 2011. This is realistic as each of the six OPUS teams discharges approximately 40 to 50 patients per year.

### Ethical considerations

The result of this trial can be of great importance for future health-care planning to benefit people with a first-episode psychosis. The extended treatment period will, as mentioned earlier, be tailored to meet the patient's individual needs, witch means monitoring the treatment intensity up and down to support the patient's empowerment and recovery process. The design of the trial does not put participants at any unacceptable level of risk and the trial design uses the best form of standard care as the control group intervention.

### Informed consent

All potential participants considered for this trial will be provided with written and oral information on this trial so that they can make an informed decision about their participation. The participants must sign this consent form before being randomized. This protocol was submitted the Regional Ethics Committees for The Capital Region for review (journal no H-C-2009-035). The Committee assessed the protocol to be exempt from formal approval with the reason that the trial is a non-biomedical trial. For further detail information please contact: http://www.cvk.sum.dk

The participants will be offered written information about the findings and the results after analysing the OPUS II trial. The information is offered in form of a standard letter and will be posted to those who sign up for this opportunity.

The OPUS II trial has permission from the Danish Data Protecting Agency: J. no. 2009-41-3314 and is publicly registered (Clinical Trial Gov Identifier no.: NCT 00914238).

## Discussion

The strengths of the OPUS II trial is the high internal and external validity[23]. The use of a computer generated random sequence generation handled by an external partner (the Copenhagen Trial Unit) reduces the risk of selection bias. Secondly, the use of blinded outcome assessors for the primary outcome and the use of intention-to-treat analysis aim to prevent biased effect estimate[23].

The publication of the current design article and registration of the trial at 'clinical.trials.gov' are intended to prevent selective outcome reporting. The risk of spurious findings, random error, is reduced, in case the pre-specified sample size is reached.

The fact that we are not able to blind the participants and personnel in the extension period of OPUS treatment might increase the risk of performance bias. Due to the novelty and excitement of participating in a research project it could be argued, that both participants and staff conducting the experimental intervention would be more enthusiastic and keen to perform well and thereby offer a higher level of OPUS treatment than the actual intervention itself.

All potential patients in the catchments area are approached and offered OPUS II treatment and together with few exclusion criteria it provides a high level of external validity. However, the educational requirements for OPUS staff are a potential limitation to less developed health-care services.

Negative symptoms as measured with SANS are the primary outcome measure for this trial. Negative symptoms are associated to the patients experience of quality of life and the level of social functions[24,25], and therefore is likely to have a great impact on peoples live through interference with their social and educational lives. Furthermore, negative symptoms have been shown to have higher prognostic value than psychotic symptoms[26,27].

A further strength of our trial is our aim to monitor program fidelity and to address the presence or absence of critical components in the OPUS treatment. Currently, no single accepted validated standard to measure the program fidelity of first episode psychosocial treatment exists, and we hope to be able to contribute to the establishment of such a standard.

## Abbreviations

ACT: Assertive Community Treatment; CTU: Copenhagen Trial Unit; CSQ: Client Satisfaction Questionnaire; DUP: Duration of Untreated Psychosis; GAF: Global Assessment of Functioning; ICC: Interclass Correlation Coefficient; IFAC T: Index of Fidelity of Assertive Community Treatment; OPUS: is not an abbreviations, OPUS is a name borrowed from the world of music; PSP: Personal and Social Performance scale; QOL: Quality Of Life; SANS: Schedule for Assessment of Negative symptoms in Schizophrenia; SAPS: Schedule for Assessment of Positive symptoms in Schizophrenia; SCAN: Schedules for Clinical Assessment in Neuropsychiatry; UKU: Side effect rating scale; WAI: Working Alliance Inventory;

